## Abstract

**Background:**

Recent developments in large bowel surgery are the introduction of laparoscopic surgery and the implementation of multimodal fast track recovery programs. Both focus on a faster recovery and shorter hospital stay.

The randomized controlled multicenter LAFA-trial (LAparoscopy and/or FAst track multimodal management versus standard care) was conceived to determine whether laparoscopic surgery, fast track perioperative care or a combination of both is to be preferred over open surgery with standard care in patients having segmental colectomy for malignant disease.

**Methods/design:**

The LAFA-trial is a double blinded, multicenter trial with a 2 × 2 balanced factorial design. Patients eligible for segmental colectomy for malignant colorectal disease *i.e*. right and left colectomy and anterior resection will be randomized to either open or laparoscopic colectomy, and to either standard care or the fast track program. This factorial design produces four treatment groups; open colectomy with standard care (a), open colectomy with fast track program (b), laparoscopic colectomy with standard care (c), and laparoscopic surgery with fast track program (d). Primary outcome parameter is postoperative hospital length of stay including readmission within 30 days. Secondary outcome parameters are quality of life two and four weeks after surgery, overall hospital costs, morbidity, patient satisfaction and readmission rate.

Based on a mean postoperative hospital stay of 9 +/- 2.5 days a group size of 400 patients (100 each arm) can reliably detect a *minimum *difference of 1 day between the four arms (alfa = 0.95, beta = 0.8). With 100 patients in each arm a difference of 10% in subscales of the Short Form 36 (SF-36) questionnaire and social functioning can be detected.

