### Study design

The LAFA-trial is a randomized multicenter trial, designed as a 2 × 2 balanced factorial design. Patients are blinded for the type of intervention *i.e*. laparoscopic or open surgery. Patients eligible for segmental colectomy, for malignant colorectal disease *i.e*. right and left colectomy and anterior resection will be randomized to either open or laparoscopic colectomy, and to either standard care or the fast track program. This factorial design results in four treatment groups; open colectomy with standard care (a), open colectomy with fast track perioperative care (b), laparoscopic colectomy with standard care (c), and laparoscopic surgery with fast track perioperative care (d) (see Figure 1).

Randomization is performed by an Internet randomization module. Block-randomization is used and the randomization is stratified for the randomizing centers.

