### Study outline

Informed consent will be obtained at the outpatient department if the patient fulfills the inclusion and exclusion criteria. Randomization is performed instantly through the study website.

The randomization produces four treatment groups; open colectomy with standard care (a), open colectomy with fast track perioperative care (b), laparoscopic colectomy with standard care (c), and laparoscopic surgery with fast track perioperative care (d) (see Figure 1).

Patients that are randomized to fast track perioperative care will be informed by a "fast track" trial nurse and by the anesthesiologist about the essence of the fast track program. Appointments for these consultations will be made after consulting the surgeon and randomization has been done. All patients randomized to have a fast track perioperative treatment will be admitted to a separate "fast track" ward, where the nurses and medical staff are trained in fast track perioperative management.

Patients who will receive standard treatment are not counseled by the fast track nurse and will have a standard preassessment by the anesthesiologist.

Patient and medical staff will be blinded for the surgical approach until the day of discharge by applying a covering abdominal bandage.

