#### Discharge criteria

Since hospital stay is a primary efficacy parameter, the discharge criteria are defined. Every postoperative day will be noted whether the discharge criteria are met, and other reasons of prolonged hospital stay *e.g*. social environment or patient in acceptance. The discharge criteria include adequate pain control with oral analgesics, no nausea, ability to take solid foods, passage of flatus and/or stool, mobilization and self support as compared to the preoperative level, and acceptance by the patient.

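### The abstract calls the whole trial double blinded, but only the surgical approach is masked, and only until discharge; fast track v standard care is open, and its effect on stay can reflect discharge practice as well as recovery

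*Protocol article*

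**What the plan says.** The Methods/design paragraph of the abstract says, without naming a factor, that "The LAFA-trial is a double blinded, multicenter trial".

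The body is narrower. Under Study design, "Patients are blinded for the type of intervention", which that sentence goes on to define as laparoscopic or open surgery. Under Study outline, "Patient and medical staff will be blinded for the surgical approach until the day of discharge by applying a covering abdominal bandage".

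For the care factor, Study outline describes open delivery:
- "Patients that are randomized to fast track perioperative care will be informed by a" dedicated trial nurse and by the anesthesiologist.
- "Patients who will receive standard treatment are not counseled by the fast track nurse".
- Fast track patients lie on a separate ward, "where the nurses and medical staff are trained in fast track perioperative management".

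The section on fast track and standard care adds that nurses with fast track experience may not nurse standard care patients.

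The primary endpoint is total postoperative stay in days, including days of readmission within 30 days. Quality of life at two and four weeks is secondary. Under Discharge criteria, "Every postoperative day will be noted whether the discharge criteria are met", together with other reasons for a prolonged stay. The criteria end with "mobilization and self support as compared to the preoperative level, and acceptance by the patient". Time to meeting the criteria is not in the list of endpoints.

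**The concern.** A reader of the abstract will take both factors to be protected by masking. One is not, and it is the one closer to the discharge decision. Counselling before surgery is given to one care arm only, and it can change what a patient expects and accepts. Separate wards keep the two care programs apart, but they also allow two different discharge habits to develop.

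The primary endpoint is the day the patient leaves, not the day the patient is fit to leave. A shorter stay under fast track could therefore come from faster recovery, from a shorter interval between fitness and discharge, or from both. The same holds for combination v current treatment, which also crosses the open factor.

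The Background and the sample size section justify stay as an endpoint through earlier recovery, so the distinction affects what the trial can conclude. It also bears on the aim, set out in the Discussion, of weighing the contribution of each method to the reduction in stay: a masked factor would be compared with an open one under a single label.

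**Working it through.** **1. Who is masked to what**

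| | Surgical approach | Fast track v standard care |
|---|---|---|
| Patients, in hospital | masked by bandage | open (counselling, ward) |
| Ward staff, in hospital | masked by bandage | open (separate trained staff) |
| Patients, after discharge | masking has ended | open |

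The label in the abstract fits the first column up to discharge and nothing else.

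**2. Quality of life**

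The protocol gives a mean stay of 9 days and an SD of 2.5 days for standard care at one center. Two weeks lies (14 − 9)/2.5 = 2 SD above that mean. Whatever the shape of the distribution, at most 1/(1 + 2²) = 20% of patients can lie 2 SD or more above the mean. So at least 80% would be discharged, and unmasked, before the two-week questionnaire, and more before the four-week one. This assumes that the mean and SD hold in the trial.

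**3. The plan's own power**

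Inputs from the sample size section: SD 2.5 days, difference 1 day, 5% level (taken as two-sided, since sidedness is not stated), 400 patients. That is 200 v 200 for each factor and 100 v 100 for combination v current treatment.

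SE = 2.5 × √(2/n); power = Φ(δ/SE − 1.96) + Φ(−δ/SE − 1.96).

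- n = 200: SE = 0.25; 1/0.25 = 4.00; power = Φ(2.04) = 97.9% (stated: above 95%).
- n = 100: SE = 0.354; 1/0.354 = 2.83; power = Φ(0.87) = 80.7% (stated: 80%).

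Both figures reproduce. The problem is one of bias, not of power.

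**4. What a shift in discharge timing alone would do**

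Assume no difference in recovery and a mean shift of b days in the time from fitness to discharge. Put b in place of δ in the same formula. The documents give no value for b, so a range is shown.

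| Assumed shift b (days) | Chance of p<0.05, 200 v 200 | Chance of p<0.05, 100 v 100 |
|---|---|---|
| 0.25 | 17% | 11% |
| 0.50 | 52% | 29% |
| 0.75 | 85% | 56% |
| 1.00 | 98% | 81% |

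The smallest observed difference that reaches significance is 1.96 × 0.25 = 0.49 day for 200 v 200, and 1.96 × 0.354 = 0.69 day for 100 v 100.

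**The case against.** The label is one phrase in an abstract. The body limits masking to the surgical approach wherever it describes it, and nowhere claims that perioperative care or quality of life is blinded. That stands, and it makes the first part of the remedy a matter of wording. It does not make the abstract correct.

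Counselling and a trained ward belong to the fast track program. If the question is how the care strategies compare on hospital stay, part of a shorter stay reached through counselling and ward practice is an effect of the package. This also stands: actual stay is a legitimate primary endpoint. What it does not show by itself is faster recovery.

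The plan has safeguards. One set of discharge criteria applies to all arms. Reasons for delay, including non-acceptance by the patient, are logged each day. Readmission days count toward the endpoint, so discharging too early carries a penalty if the patient returns. The plan also names staff bias toward fast track and separates the wards because of it. The first three reduce the problem. Separate wards limit contamination but mask nobody, and no assessor unaware of the care arm is described.

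The chance of 98% at a 1-day shift is the design power under another name, since any 1-day difference from any cause gives it. That is correct, and it is why a range is shown.

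Finally, analysis of the daily record may be set out in a fuller document that is not shown. Its absence here is therefore not called an omission; the proposal is an improvement to the list of endpoints that the article gives.

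**Conclusion.** The abstract attributes to the whole trial a property that the design has for one factor only, in hospital only. The comparisons exposed are fast track v standard care and combination v current treatment on stay, and both factors on quality of life. Laparoscopic v open stay within a care arm is protected by the bandage.

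The size of any bias is unknown. With SD 2.5 and 200 v 200, an assumed pure timing shift of half a day would give significance in about half of trials, and a quarter of a day in about one in six.

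A reader might infer that the endpoint will in fact move by a day, or that a fast track effect on recovery could never be told apart from discharge habits. The documents support neither. No lag between fitness and discharge is reported for either ward type, and the daily record offers a way, if an imperfect one, to separate the two.

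**What to change.** 1. In the abstract, replace the double-blind label with: *patients and medical staff masked to surgical approach until discharge; perioperative care open*.
2. Pre-specify, as a secondary endpoint for both factors, the first postoperative day on which the discharge criteria are recorded as met, taken from the daily record already planned. Separate out patient acceptance where the logged reasons for delay allow it. The article does not say that each criterion is recorded singly, so this needs checking against the data collection module.
3. Report this endpoint beside length of stay whenever a fast track effect is interpreted as faster recovery. No formal rule that the two must agree is needed.

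The discharge criteria and the primary endpoint stay as they are. The cost is a change of wording and one extra analysis. The limit is that staff who know the care arm still record the criteria, so the bias is reduced, not removed.

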**Discussion:**

The LAFA-trial is a randomized controlled multicenter trial that will provide evidence on the merits of fast track perioperative care and laparoscopic colorectal surgery in patients having segmental colectomy for malignant disease.

## Background

Recent developments in large bowel surgery are the introduction of laparoscopic surgery and the implementation of multimodal fast track perioperative care programs. Both focus on enhanced recovery and shorter hospital stay as compared to open surgery and traditional care. Laparoscopic colectomy was first described in 1991[1]. Since then a lot of effort has been made to establish its feasibility and safety particularly in laparoscopic colectomy for cancer. Recently, several randomized trials comparing laparoscopic with open colectomy indicated that laparoscopic surgery can be applied safely both for malignant and benign diseases [2-7]. Several systematic reviews that assessed the evidence on the laparoscopic approach for colorectal cancer reported that laparoscopic surgery, in a traditional perioperative care setting was associated with less morbidity, less postoperative pain, earlier recovery and shorter hospital stay[2,8,9]. Furthermore, short term cancer related outcomes such as cancer free resection margins and the number of harvested lymph nodes, as well as long term cancer related outcomes such as disease free survival were comparable between laparoscopic and open surgery[2]. These results stimulated many surgeons in the Netherlands to set up a laparoscopic colorectal program.

At the same time, enthusiasm was raised for the so-called fast track perioperative care program, also referred to as Enhanced Recovery After Surgery (ERAS^®^), which essentially is a modification of the program initially developed by the Danish surgeon Henrik Kehlet [10-13]. This multimodal program, involving optimalization of several aspects of the perioperative management of patients undergoing colectomy, enables patients to recover earlier and therefore go home as early as three days after open colectomy. Furthermore, postoperative morbidity was reduced [14-19]. The essence of a fast track perioperative care program consists of extensive preoperative counseling, no bowel preparation, no sedative premedication, no preoperative fasting but carbohydrate loaded liquids until two hours prior to surgery, tailored anesthesiology encompassing thoracic epidural anesthesia and short acting anesthetics, perioperative intravenous fluid restriction, minimally invasive surgery (*i.e*. through small incisions or laparoscopy), non-opioid pain management, no routine use of drains and nasogastric tubes, early removal of bladder catheter, standard laxatives and prokinetics, and early and enhanced postoperative feeding and mobilization [10-19].

As these new developments have been introduced in clinical practice, time has come to evaluate their feasibility, safety, and cost-effectiveness in large bowel surgery in a randomized controlled setting. It can be hypothesized that fast track and/or laparoscopy are associated with less attenuation of the patient's condition after surgery resulting in a shorter postoperative hospital stay, a faster recovery to full activity at home, and a better quality of life.

Since it has not been established which combination of perioperative management and surgical approach *i.e*. standard care, fast track care, laparoscopic surgery or open surgery is best in terms of postoperative hospital stay, quality of life, postoperative morbidity, readmission rate, overall costs and patient satisfaction, this is the subject of the present study proposal.

## Methods/design

### Study objectives

The objective of this study is to determine whether laparoscopic surgery, fast track perioperative care or a combination of both is to be preferred over open surgery with standard care in patients undergoing segmental colectomy for malignant disease. The objective is subdivided in three research questions; first, how laparoscopic surgery compares to open surgery in terms of hospital stay, quality of life and costs? Second, how fast track perioperative care compares to standard care in terms of hospital stay, quality of life, and costs? Finally, what is the added benefit of fast track perioperative care program in laparoscopic surgery in terms of hospital stay, quality of life and costs?

### Study design

The LAFA-trial is a randomized multicenter trial, designed as a 2 × 2 balanced factorial design. Patients are blinded for the type of intervention *i.e*. laparoscopic or open surgery. Patients eligible for segmental colectomy, for malignant colorectal disease *i.e*. right and left colectomy and anterior resection will be randomized to either open or laparoscopic colectomy, and to either standard care or the fast track program. This factorial design results in four treatment groups; open colectomy with standard care (a), open colectomy with fast track perioperative care (b), laparoscopic colectomy with standard care (c), and laparoscopic surgery with fast track perioperative care (d) (see Figure 1).

Randomization is performed by an Internet randomization module. Block-randomization is used and the randomization is stratified for the randomizing centers.

### Primary and secondary endpoint

The primary endpoint of the LAFA-study is total postoperative hospital stay in days, including hospital stay of patients who are readmitted within 30 days after surgery.

Secondary endpoints are quality of life at two and four weeks after surgery. Quality of life will be measured by two validated questionnaires; Short Form 36 (SF-36) and the Gastro-Intestinal Quality of Life Index (GIQLI). Further secondary endpoints are; medical and non medical costs, morbidity, and mortality within 30 days after surgery, patient satisfaction measured by standardized questionnaires, and readmission rate.

### Participating centers

Seven Dutch hospitals of the LAFA-study group, including three academic centers and four non-academic centers, will enroll patients.

### Study population

The study population consists of patients eligible for segmental colectomy for malignant colorectal disease viz. right and left colectomy and anterior resection.

Inclusion criteria are; age between 40 and 80 years, colorectal cancer including colon and recto sigmoid cancers, ASA I-III, and informed consent.

Exclusion criteria are; prior midline laparotomy, ASA IV, laparoscopic surgeon not available, emergency surgery and a planned stoma.

### Ethics

This study is conducted in accordance with the principles of the Declaration of Helsinki and 'good clinical practice' guidelines. The independent medical ethics committees of the participating hospitals have approved the study protocol. Prior to randomization, written informed consent will be obtained from all patients.

### Study outline

Informed consent will be obtained at the outpatient department if the patient fulfills the inclusion and exclusion criteria. Randomization is performed instantly through the study website.

The randomization produces four treatment groups; open colectomy with standard care (a), open colectomy with fast track perioperative care (b), laparoscopic colectomy with standard care (c), and laparoscopic surgery with fast track perioperative care (d) (see Figure 1).

Patients that are randomized to fast track perioperative care will be informed by a "fast track" trial nurse and by the anesthesiologist about the essence of the fast track program. Appointments for these consultations will be made after consulting the surgeon and randomization has been done. All patients randomized to have a fast track perioperative treatment will be admitted to a separate "fast track" ward, where the nurses and medical staff are trained in fast track perioperative management.

Patients who will receive standard treatment are not counseled by the fast track nurse and will have a standard preassessment by the anesthesiologist.

Patient and medical staff will be blinded for the surgical approach until the day of discharge by applying a covering abdominal bandage.

#### Surgery

Both open and laparoscopic surgery is done according to the technique applied by the local surgeon. Antibiotic prophylaxis is done according to hospital protocol. All patients will have two enemas before surgery (evening before and morning before). After surgery the surgical wounds are covered with a abdominal dressing in order to blind the medical staff for the type of approach. A requirement for the participating laparoscopic surgeons to perform laparoscopic colectomy for cancer is a minimum of 20 laparoscopic colectomies for benign disease as indicated by the proclamation of the American Society of the Colon and Rectum Surgeons in 2004[20,21].

#### Fast track and standard care

Comparison of the different strategies is only possible when a fast track program is running sufficiently and patients are nursed separately depending on the results of randomization either on a standard care or fast track ward in order to avoid a bias towards fast track treatment by the nursing and medical staff. Patients that have standard care cannot be nursed by nurses that have experience with fast track care. Fast track multimodal management is done according to the protocol summarized in Table 1.

#### Discharge criteria

Since hospital stay is a primary efficacy parameter, the discharge criteria are defined. Every postoperative day will be noted whether the discharge criteria are met, and other reasons of prolonged hospital stay *e.g*. social environment or patient in acceptance. The discharge criteria include adequate pain control with oral analgesics, no nausea, ability to take solid foods, passage of flatus and/or stool, mobilization and self support as compared to the preoperative level, and acceptance by the patient.

### Statistical analysis

#### Intention to treat

The analysis will be performed in accordance with the intention to treat principle.

#### Sample size calculation

Since both, fast track care and laparoscopy focus on earlier recovery resulting in a reduction of hospital stay, the latter is used as primary efficacy parameter. The mean postoperative hospital stay for segmental bowel resection with standard care is 9 days with a standard deviation of 2.5 days in the Academic Medical Center Amsterdam. Using a 5% significance level, a total sample size of 400 would have a power of >95% to detect a minimum reduction of 1 day in hospital stay between laparoscopic surgery and open surgery, a 1 day reduction in hospital stay between fast track care and standard care, and a power of 80% to detect the same difference between the combination of fast track care with laparoscopic surgery and current treatment.

A much larger difference can be expected between the treatment groups, for instance open surgery and standard care compared to fast track perioperative care and laparoscopic surgery. In order to obtain results with adequate precision we have calculated group size using a difference of 1 day rather than the expected 2–4 days. With a group size of one hundred patients per arm it is possible to find a significant difference (alfa = 0.05, beta = 0.1) of at least 10% in subscales of the SF-36, a validated Quality of life Questionnaire, at two weeks after surgery [22-24]. Liem *et al*. demonstrated 20–30% differences in subscales of the SF-36 between laparoscopic versus open hernia repair 1 week after surgery[24]. Maartense *et al*. found a 10% difference in physical and social function two weeks after surgery comparing laparoscopic versus open ileocolic resection in a randomized study from our institution[25].

